**Protocol**

**Study objective**

***Primary objective:*** To compare rates of post-ERCP pancreatitis (PEP) between the intravenous albumin-administered plus high-volume lactated Ringer solution (LRS) group and standard LRS infusion group

***Secondary objectives:***

1. To compare rates of pancreatic enzyme elevation between the intravenous albumin-administered plus high-volume LRS group and standard LRS infusion group
2. To compare rates of fluid overload between the intravenous albumin-administered plus high-volume LRS group and standard LRS infusion group

**Study design and setting**

***Design:*** Parallel-arm randomised controlled trial (RCT) – participants and outcome assessors blined

***Setting:*** Vajira Hospital (Navamindradhiraj University)

**Inclusion criteria**

- Age ≥ 18 years
- Have pancreatobiliary diseases requiring ERCP
- Willing to participate

**Exclusion criteria**

- Have a history of congestive heart failure
- Have signs of fluid overload
- Suffer significant comorbidities
  - CKD stage ≥ 3
  - Decompensated cirrhosis
  - COPD
- Suffer active pancreatitis
- Unstable hemodynamics
- Allergy to human albumin

**Intervention**

Bolus fluid will be calculated to have a volume of 15 ml/kg of LRS. Then, 600 ml of this volume will be replaced with 50 ml of 20% human albumin^1,2^ and started ~ 1 h prior to procedure. The rest of the bolus fluid will be given subsequently. LRS will be administered at a rate of 3 ml/kg/h until 8 h post-ERCP, followed by the maintenance rate. Ideal body weight will be used in fluid calculation (for both intervention and control groups) if pariticipants weigh > 80 kg.

**Control**

LRS will be administered at a fixed rate of 1.5 mL/kg/h and started approximately at 1 h before ERCP.

**Co-interventions**

***ERCP procedure:***

ERCP will be performed under general anesthesia with prone or supine position depended on endoscopist preference. Steps of the procedure include selective bile duct cannulation, sphincterotomy, complete cholangiography, and therapeutic interventions regarding pathology. These steps can be modified and varied between cases as needed. Before termination, the rest of contrast media will be removed as much as possible. All participants will be discharged home after 24 h if uneventful.

***Antibiotic:***

Prophylactic antibiotic will be the 3^rd^ generation cephalosporins – ceftriaxone – if there is no history of drug allergy. Participants who require antibiotic for therapeutic indications will receive empirical antibiotics such as cephalosporins, carbapenams, or piperacillin/tazobactam and de-escalate later as indicated.

***Other treatments:***

Treatment will be reconciled with participant’s underlying conditions. If adverse events developed, treatments would be delivered regarding a standard guideline. This includes aggressive intravenous fluid in case of PEP.

**Outcomes and measurement**

***Primary outcome:***

PEP will be diasnosed if participants develop acute epigastrium pain within 24 h after ERCP accompanying with elevated serum amylase or lipase levels. Definition of elevated pancreatic enzyme is a serum level > 3 times higher than the upper normal limit (>300 U/L for and >180 U/L for amylase and lipase, respectively). Signs and symptoms will be evaluated every 6 h until 24 h after ERCP by physicians blinded to allocation. Blood will be drawn for pancreatic enzyme measurement at 4 and 24 h after ERCP. This outcome will be analysed as a binary endpoint.

***Secondary outcome:***

1. Elevated serum pancreatic enzyme level: will be measured at 4 and 24 h after ERCP. Definition of this outcome is described as above. This outcome will be analysed as a binary endpoint (the occurrence of elevated enzyme level within 24 h after ERCP).
2. Fluid overload: any dyspnea with crackle sounds from chest auscultation and peripheral edema will be recorded. This outcome will be analysed as a binary endpoint.
3. Other complications and mortality: the number of each event will be records separately.

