**Sample size estimation**

The Park et al’s study^3^ has indicated that rates of PEP in aggressive and standard volume intravenous fluid was 3% and 11.6%, respectively. Based on these findings, 286 participants would be enrolled for the current study given alpha-error, power, and allocation ratio of 5%, 20%, and 1:1, respectively. To compensate for enrolment error that might occur, 300 participants will be recruited.

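### The secondary enzyme outcome has no pre-ERCP value and no new-onset condition, so elevations present before ERCP that persist count as events in both arms and pull its risk ratio towards 1

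*Protocol*

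**What the plan says.** Under Primary outcome the protocol sets the enzyme rule: "Definition of elevated pancreatic enzyme is a serum level > 3 times higher than the upper normal limit", given as more than 300 U/L for amylase and 180 U/L for lipase. The sampling schedule is "Blood will be drawn for pancreatic enzyme measurement at 4 and 24 h after ERCP". PEP is diagnosed if participants "develop acute epigastrium pain within 24 h after ERCP accompanying with elevated serum amylase or lipase levels".

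Under Secondary outcome the same cut-off and sampling times are reused, and the binary endpoint is "the occurrence of elevated enzyme level within 24 h after ERCP". No pain is needed for this one.

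Entry is open to patients who "Have pancreatobiliary diseases requiring ERCP". The only exclusion that bears on enzymes is "Suffer active pancreatitis", with no enzyme threshold attached. The protocol nowhere asks for an amylase or lipase value before ERCP, or for a rise from such a value.

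The sample size section plans on PEP alone: "rates of PEP in aggressive and standard volume intravenous fluid was 3% and 11.6%, respectively", with 286 participants required and 300 recruited. The Statistical analysis section names the risk ratio as the effect measure.

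**The concern.** The secondary outcome is meant to show whether the fluid regimen changes pancreatic enzyme elevation after ERCP. A level that was above the cut-off before any study fluid was given, and has not yet fallen, says nothing about that, yet it is scored as an event. Such events occur at about the same rate in both arms, so they add a constant to both rates. The ratio of the rates moves towards 1, and a real benefit looks smaller on the scale the protocol reports.

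The exclusion of active pancreatitis helps but does not clearly close the gap, because elevation without pain, or elevation that is resolving, need not count as active pancreatitis.

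This is not a detail that a statistical analysis plan can supply later. The protocol fixes both the definition and the blood draws, and an unrecorded baseline value cannot be recovered at analysis.

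**Working it through.** **1. The plan's own figure.** Inputs from Sample size estimation: p1 = 0.03, p2 = 0.116, alpha 5%, 1:1. The protocol writes "given alpha-error, power, and allocation ratio of 5%, 20%, and 1:1, respectively". The 20% reproduces the sample size only if read as the type II error, that is, 80% power; 20% power would need 48 participants. With the two-sided formula without continuity correction and mean rate 0.073:

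n = [1.960·√(2·0.073·0.927) + 0.842·√(0.03·0.97 + 0.116·0.884)]² / 0.086² = 142.4, so 143 per arm and 286 in total. This matches.

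**2. Model for the dilution.** Let q be the share of participants, equal in both arms, who are scored as events whatever the treatment. Then

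- observed rate p′ = q + (1 − q)·p
- observed risk difference = (1 − q)·(p2 − p1)
- observed risk ratio = [q + (1 − q)p1] / [q + (1 − q)p2], which moves towards 1 as q grows.

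The documents give no value for q, so every figure below is a range over assumed values.

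**3. Secondary enzyme outcome.** Here q is the share above the cut-off before ERCP and still above it at 4 or 24 h. The true rates are also not in the documents. Assume 25% v 12.5% and q = 5%:

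- p2′ = 0.05 + 0.95·0.25 = 0.2875
- p1′ = 0.05 + 0.95·0.125 = 0.16875
- risk ratio 0.16875/0.2875 = 0.59, against 0.50 without dilution
- risk difference 11.9 points, against 12.5
- exact chi-square power at 150 per arm 69.4%, against 80.2%.

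Other assumed rates, with power at 150 per arm by the normal approximation:

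| True rates | q | Risk ratio | Power |
|---|---|---|---|
| 30% v 15% | 0 | 0.50 | 87.9% |
| 30% v 15% | 5% | 0.58 | 80.3% |
| 30% v 15% | 10% | 0.64 | 72.3% |
| 20% v 10% | 0 | 0.50 | 68.1% |
| 20% v 10% | 5% | 0.60 | 55.1% |
| 20% v 10% | 10% | 0.68 | 45.1% |

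The trial states no power for this outcome, so these figures show the mechanism and not a shortfall against a plan.

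If the outcome instead required new elevation, with the high-baseline participants kept as non-events, the first example would give 0.95·0.125 = 0.11875 and 0.95·0.25 = 0.2375. The ratio returns to 0.50.

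**4. PEP.** Here q is the share who become false PEP events: high before ERCP, not excluded, still high afterwards, and with epigastric pain developing within 24 h. Power is by exact binomial enumeration of the two-sided uncorrected chi-square test at 150 per arm.

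| q | Rates | Risk ratio | Risk difference | Exact power at 300 |
|---|---|---|---|---|
| 0 | 3.0% v 11.6% | 0.26 | 8.6 points | 84.2% |
| 1% | 4.0% v 12.5% | 0.32 | 8.5 | 78.4% |
| 2% | 4.9% v 13.4% | 0.37 | 8.4 | 73.2% |
| 3% | 5.9% v 14.3% | 0.41 | 8.3 | 68.4% |
| 4% | 6.9% v 15.1% | 0.45 | 8.3 | 63.9% |

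Exact power crosses 80% at q of about 0.7%. The normal approximation starts lower (82.0% at q = 0) and is already at 79.4% at q = 0.5%, so the crossing point depends somewhat on the method.

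**5. From baseline elevation to false PEP.** q = (share with persisting baseline elevation) × (share of these who develop pain). Both are assumed:

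- 3% × 10% = 0.3%: power 82.3%
- 3% × 20% = 0.6%: power 80.6%
- 3% × 30% = 0.9%: power 78.9%
- 5% × 20% = 1%: power 78.4%
- 10% × 20% = 2%: power 73.2%

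To reach q = 4% with a 20% pain share, 20% of all participants would need a persisting baseline elevation.

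**The case against.** The strongest reply is that the effect is conservative, of unknown size, and small where it matters most. Much of this stands.

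- A reader might infer that the primary outcome is compromised, and planned power lost, as soon as a few percent of participants have raised enzymes at entry. The documents do not support that. PEP needs pain that develops after ERCP as well, and 3% with raised enzymes and a 20% pain share leaves exact power at 80.6%.
- A reader might infer that anyone with high enzymes at entry is bound to be an event. That is too strong: a level that has fallen below the cut-off by 4 h is not counted.
- A reader might infer bias for or against the albumin arm. Randomisation balances the baseline share on average, so the result is dilution, and the risk difference shrinks only by the factor 1 − q.
- The PEP power figures assume that the 3% and 11.6% planning rates contain no such events. If the cited trial also judged enzymes without a baseline condition, those rates may already include them, and the same share would cost no planned power. The documents do not say.
- Requiring new elevation inside the PEP definition would mean that a participant with a high baseline who develops true pancreatitis could never be a case. That trades possible false positives for certain false negatives, and is a reason to leave the primary definition alone.
- A sensitivity analysis could be left to a statistical analysis plan. That is true of the analysis, but not of the blood value it needs.

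None of this answers the point for the secondary outcome, where no pain is required and a persisting baseline elevation is enough.

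**Conclusion.** The point holds for the secondary enzyme outcome. As defined, it counts elevation that was present before ERCP and persists, in either arm, and nothing in the eligibility criteria clearly removes it. The result is a risk ratio pulled towards 1 and some loss of precision: for example 0.50 to 0.59 at a 5% persisting baseline share under assumed true rates of 25% v 12.5%. The size rests wholly on assumed values.

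For PEP the effect is smaller and conditional. It brings exact power at 300 below 80% only if false PEP events exceed about 0.7% of participants, and only if the planning rates are free of such events. The documents fix neither the baseline share nor the pain share, so no statement that the primary analysis is underpowered for this reason can be made. This is a worthwhile, inexpensive improvement and not a defect that threatens the primary comparison.

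**What to change.** - Record one amylase/lipase value before the study infusion starts. It can be added to the pre-ERCP blood or taken from the result used to rule out active pancreatitis. Allocation is revealed during admission the day before ERCP, so participants are already in hospital and no visit is added.
- Define the secondary enzyme outcome as new elevation: above the cut-off at 4 or 24 h and not above it before.
- Leave the primary PEP definition as it is. Add a sensitivity analysis of PEP without participants whose pre-ERCP value was already above the cut-off. Because the value precedes treatment, the arms in that analysis remain a randomised comparison.

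Cost: at most one extra assay per participant (up to about 300), less where an existing result is used, plus one sentence in the outcome definition and one in the analysis section. The drawback is that participants with high baseline values can no longer contribute a secondary enzyme event.

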**Consent**

Patients required ERCP will be admitted to the hospital. Researchers will screen for eligible patients and invite to participate in this study. Details of the study including rationales, benefits, and risks will be thoroughly informed. Patients will be informed that their decision will not affect on their treatments, and they can withdraw from the study at any time. Written informed consent will be obtained from participants who are willing to participate.

**Randomisation and concealment**

A permuted block randomisation with varying block size (4-8 participants per block), 1:1 allocation ratio, will be used to generate random sequence list. This sequence will be concealed with sequentially numbered, opaque, sealed envelopes, which will be revealed during admission at 1 day before ERCP. Random sequence list and envelopes will be prepared by statisticians who will not involve in this study.

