**Blinding**

Participants and outcome assessors will be blinded to the treatment allocation. Also, physician team, except endoscopists, will be blinded. Physician team will be unblinded in case a knowledge of treatment allocation is necessary, for example, PEP.

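### Allocation is opened the day before ERCP although study fluid starts only about 1 h before it, leaving an avoidable gap for post-randomisation loss (minor, cheap to improve)

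*Protocol*

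**What the plan says.** - **Reveal.** Protocol, Randomisation and concealment, on the envelopes: "which will be revealed during admission at 1 day before ERCP". The section does not say to whom the allocation is revealed.
- **Start of study fluid.** In the intervention arm the first fluid is "started ~ 1 h prior to procedure" (Intervention). In the control arm it is "started approximately at 1 h before ERCP" (Control).
- **Who is blinded.** Participants and outcome assessors are. The Blinding section adds: "Also, physician team, except endoscopists, will be blinded".
- **What can change in between.** Consent tells patients that "they can withdraw from the study at any time". The Exclusion criteria include conditions that may arise within a day, for example "Unstable hemodynamics", and also active pancreatitis and signs of fluid overload.
- **When the primary outcome can occur.** Participants must "develop acute epigastrium pain within 24 h after ERCP" (Primary outcome), together with raised enzymes.
- **Allowance.** After deriving 286, Sample size estimation says: "To compensate for enrolment error that might occur, 300 participants will be recruited".

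The protocol gives no reason for the early reveal, no eligibility re-check when fluid starts, and no rule for a randomised patient whose ERCP does not go ahead.

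**The concern.** Randomisation should come as close as practicable to the point where the arms diverge. Here they diverge at the first infusion, yet the allocation is opened roughly a day earlier. Two things are at stake.

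1. **Avoidable loss.** A patient who is randomised and then has no ERCP cannot develop post-ERCP pancreatitis as defined. Analysing by allocated arm does not recover that observation, because there is nothing to observe. Only later randomisation prevents the loss.
2. **Opportunity for selection.** If someone with a say in whether the procedure goes ahead knows the arm, the decision could depend on it. The two fluid regimens differ markedly in volume, so a patient whose fluid status has become doubtful overnight might be held back more readily from one arm. That would bear on the primary comparison and on fluid overload, a named secondary outcome.

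**Working it through.** **Step 1: the gap.** Reveal is 1 day before ERCP; fluid starts about 1 h before. If 1 day is read as 24 h, the gap is 24 − 1 = about 23 h, the same in both arms.

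**Step 2: reproduce the planned sample size.** Inputs from Sample size estimation: p₁ = 0.116 (standard), p₂ = 0.03 (aggressive), alpha 5%, 1:1 allocation. The section gives power as 20%. That can only be the type II error, since a literal power of 20% would need 48 in total. I take power as 80% and alpha as two-sided. With p̄ = (0.116 + 0.03)/2 = 0.073, the pooled-variance formula per arm is

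n = [1.960·√(2p̄(1−p̄)) + 0.842·√(p₁(1−p₁) + p₂(1−p₂))]² / (p₁ − p₂)²

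- √(2 × 0.073 × 0.927) = √0.13534 = 0.3679
- √(0.116 × 0.884 + 0.03 × 0.97) = √0.13164 = 0.3628
- n = (0.7210 + 0.3054)² / 0.086² = 1.0535 / 0.007396 = 142.4, rounded up to 143

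The total is 286, which matches the protocol exactly.

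**Step 3: the allowance.** 300 − 286 = 14, and 14/300 = 4.7%.

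**Step 4: power after loss.** With n per arm remaining,

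power = Φ[(0.086·√n − 0.7210) / 0.3628]

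The documents give no rate of loss between reveal and ERCP, so the rates below are assumptions, with loss taken as equal in the two arms. The last column is 286/(1 − loss), rounded up.

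| Assumed loss | Remaining of 300 | Power | To randomise to keep 286 |
|---|---|---|---|
| 0% | 300 | 82.0% | 286 |
| 2% | 294 | 81.2% | 292 |
| 5% | 285 | 80.0% | 302 |
| 10% | 270 | 77.8% | 318 |
| 15% | 255 | 75.5% | 337 |

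For example, at 10% loss: n = 135, √135 = 11.619, (0.9992 − 0.7210)/0.3628 = 0.767, and Φ(0.767) = 77.8%.

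**Step 5: the selection route.** Participants, outcome assessors and the other physicians are meant to be blinded. The people who could act on the allocation are therefore the endoscopists, if they are told early, and whoever opens the envelope. The protocol neither says they are told early nor prevents it. No size can be put on this part from the documents.

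**The case against.** The other side has several good points.

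- **Concealment up to the reveal is sound.** Block sizes vary, the envelopes are numbered, sealed and opaque, and uninvolved statisticians prepare them. Consent precedes the reveal, so entry to the trial is not biased. This stands, and the point here concerns only what happens afterwards.
- **The effect on power is small.** At losses up to about the 4.7% allowance, power stays at 80% or more. A postponed ERCP is also not necessarily a lost participant. Both stand.
- **An unseen SAP may define the analysis set.** It may, so no instruction on analysis sets is made here. But a SAP cannot move the reveal, which the protocol itself fixes, or supply an outcome for a patient who had no ERCP.
- **The endoscopist stays unblinded under any timing.** True. Later opening does not blind the procedure; it only shortens the time in which allocation could affect who reaches it.

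A reader might also infer more than the text supports:

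- *That the 14 extra patients show people are dropped after allocation.* The phrase about enrolment error is not defined, and nothing says that anyone is removed or replaced.
- *That the endoscopist knows the arm the day before.* The Blinding section says only that endoscopists are not blinded.
- *That withdrawals would follow the allocation.* Participants are blinded, so their own withdrawal is a source of loss but not, on the face of it, of selection.
- *That losing two or three patients would upset the result because few events are expected* (0.03 × 143 = 4.3 in the active arm). This compares patients with events. At the planned rates, two to three patients carry 0.06 to 0.09 expected events in the active arm (2 × 0.03 to 3 × 0.03) and 0.23 to 0.35 in control (2 × 0.116 to 3 × 0.116). The loss would matter only if it fell selectively on patients who were going to develop pancreatitis.

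**Conclusion.** The point holds as a minor, cheap improvement. The protocol opens allocation about a day before it is needed, gives no reason, and has no safeguard covering the gap. The consequence is a built-in risk of avoidable loss, with some opportunity for known allocation to influence who proceeds. Neither has been shown to occur.

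The loss component costs little: from 82.0% power with no loss to 77.8% at 10% and 75.5% at 15%, crossing 80% at about 5%. These figures rest on the protocol's own rates (3% and 11.6%), a two-sided 5% test, 80% planned power, and assumed loss rates that are equal by arm. The selection component cannot be quantified, and whether it exists at all depends on who is told the allocation, which the protocol leaves open.

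**What to change.** In Randomisation and concealment, change the time of opening to the day of ERCP, immediately before the infusion is prepared. Require confirmation first that ERCP is going ahead and that the protocol's existing exclusions are still absent. Consent and screening can stay on the day before.

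No endpoint, eligibility criterion, treatment or sample-size input changes, so 286 (300 with the allowance) stands. The cost is a change of wording and moving one step to the procedure day. The drawback is that fluids must be prepared at shorter notice.

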**Blinding**

Participants and outcome assessors will be blinded to the treatment allocation. Also, physician team, except endoscopists, will be blinded. Physician team will be unblinded in case a knowledge of treatment allocation is necessary, for example, PEP.

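### Endoscopists are exempted from blinding without a reason, although their technique is discretionary and the protocol itself treats it as bearing on the risk of post-ERCP pancreatitis

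*Protocol*

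**What the plan says.** Under Blinding, the protocol states "Participants and outcome assessors will be blinded to the treatment allocation" and then "Also, physician team, except endoscopists, will be blinded". It gives no reason for the exception. The same section already allows the physician team to be unblinded when knowing the arm is necessary.

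Under Randomisation and concealment, the allocation is in sealed envelopes, "which will be revealed during admission at 1 day before ERCP". Under ERCP procedure, after listing the steps, the protocol adds "These steps can be modified and varied between cases as needed". Under Statistical analysis, a subgroup is defined by four operator manoeuvres that the protocol calls high-risk: pancreatic duct wiring, pancreatic duct injection, precut sphincterotomy and balloon dilation of the ampulla.

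The arms differ in what is infused. In the intervention arm the bolus is 15 ml/kg, of which "600 ml of this volume will be replaced with 50 ml of 20% human albumin", and then "LRS will be administered at a rate of 3 ml/kg/h until 8 h post-ERCP, followed by the maintenance rate". In the control arm, "LRS will be administered at a fixed rate of 1.5 mL/kg/h and started approximately at 1 h before ERCP". For the primary outcome, "Signs and symptoms will be evaluated every 6 h until 24 h after ERCP by physicians blinded to allocation".

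**The concern.** The endoscopist is the one physician allowed to know the arm, and also the one whose actions can cause the primary outcome. Nothing in the protocol gives the endoscopist a part in running the fluids or another stated need to know.

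If technique differs by arm because the arm is known, the difference in PEP mixes a fluid effect with an operator effect. The enzyme criterion gives no protection, because altered technique changes true pancreatitis and not merely its recording. The high-risk subgroup has a related problem: its membership is decided by choices made after the allocation can be known. No later analysis can fully undo either effect.

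A second and weaker worry concerns the pain assessment. At 6 h the two arms are meant to be on different infusion rates, and the protocol describes no masking of bag, line or pump.

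**Working it through.** **1. Route from knowledge to outcome, from the text.**
- Knowledge: endoscopists are not blinded (Blinding), and the envelope is opened 1 day before ERCP (Randomisation and concealment). The arm can be known before the procedure.
- Freedom to act: the steps may vary between cases (ERCP procedure).
- Relevance: the protocol classes four manoeuvres as high-risk (Statistical analysis).

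No further inference is needed to conclude that performance bias is possible. Its size and direction do not follow from the text.

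**2. The plan's own sample size.** Inputs from Sample size estimation: 11.6% (standard) versus 3% (aggressive), alpha 5%, 1:1. The mean rate is (0.116 + 0.03)/2 = 0.073. With a two-sided test and 80% power:

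n per arm = [1.960·√(2·0.073·0.927) + 0.842·√(0.116·0.884 + 0.03·0.97)]² / (0.116 − 0.03)² = 142.4, rounded up to 143, or 286 in total.

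This matches the stated 286. Expected events at 143 per arm are 143 × (0.116 + 0.03) = 20.9, about 21.

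**3. Illustration of size.** The shifts are assumptions. The method is exact enumeration of two binomials with 143 per arm, Pearson chi-square without continuity correction, two-sided 5%, counting only significant results that favour the intervention.

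*No true effect; the intervention rate alone is lowered by operator behaviour:*

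| Intervention | Control | Chance of falsely declaring benefit |
|---|---|---|
| 7.3% | 7.3% | 2.3% |
| 6.3% | 7.3% | 4.9% |
| 5.3% | 7.3% | 9.7% |

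*Planned effect true; extra care lowers the control rate alone:*

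| Intervention | Control | Power |
|---|---|---|
| 3% | 11.6% | 82% |
| 3% | 10.6% | 74% |
| 3% | 9.6% | 65% |

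The 82% is the exact figure; the normal approximation used for planning gives 80.2% at the same size. One point is 143 × 0.01 = 1.4 patients in an arm.

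**4. The 6 h assessment.** Assessments every 6 h to 24 h fall at 6, 12, 18 and 24 h. The intervention rate of 3 ml/kg/h runs to 8 h, so only the first of the four falls within it. At 60 kg the stated rates are 3 × 60 = 180 ml/h and 1.5 × 60 = 90 ml/h.

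**The case against.** The strongest reply is that this is a disclosed design choice. The Study design section claims blinding only for participants and outcome assessors, and the exception for endoscopists is stated openly, so the protocol does not contradict itself. That is true. However, disclosing the exception does not remove the bias, and since unblinding on clinical need is already provided for, safety does not require a blanket exemption.

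A second reply is that any figure for the bias is chosen, not derived. That stands, and the figures above are illustrations only. A reader might move both arms in opposite directions and reach larger numbers: 8.9% for 1 point each and 24% for 2 points each. Those reproduce arithmetically, but they amount to differences of 2 and 4 points against a planned effect of 8.6. They also ignore the opposite possibility, that operators take more care with controls and dilute a real effect. The documents do not favour one direction.

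A reader might also infer that assessor blinding is broken. The protocol does not support this:
- Assessors and participants are stated to be blinded, and that the infusion is visible is an inference.
- The albumin starts about 1 h before the procedure and the rest of the bolus follows it, so nothing places either in view at 6 h.
- By then the stated difference is the rate of the same fluid, set per kg, so a displayed ml/h reveals the arm only to someone who relates it to body weight.
- No stop time is given for the control infusion, so that it is still running at 6 h is likewise assumed.
- Only one assessment in four is involved, and PEP also needs an enzyme level above three times the upper limit at 4 or 24 h. A biased pain judgement matters only in patients who meet that criterion.

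Finally, a reader might suppose that unblinded operators would vary drug prophylaxis against PEP. The protocol describes no such prophylaxis beyond the study fluids.

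**Conclusion.** The performance-bias point holds on the text alone: the exemption has no stated reason, the arm can be known before ERCP, technique is discretionary, and the protocol itself treats technique as relevant to PEP risk. The effect could go either way. Under assumed one-arm shifts of 1 or 2 points, the chance of a false claim of benefit rises from 2.3% to 4.9% or 9.7%, or power falls from about 82% to 74% or 65%. These figures rest on the planning rates, 143 per arm, the uncorrected chi-square test, and shifts that the documents neither give nor imply.

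The detection-bias point is secondary. The protocol does not say how blinding is kept at 6 h, but it does not show that blinding fails.

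**What to change.** In Blinding, delete the exception so that endoscopists are not told the allocation. In Randomisation and concealment, state that the nurse who runs the fluids opens the envelope. This should not be a member of the blinded physician team, which could include anaesthetists, because that would unblind people the protocol means to keep blinded. Add that the bag, line and pump display are covered during ERCP and at the 6 h assessment. Leave the provision for unblinding on clinical need as it is written.

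The cost is covers, a short handling instruction and some nursing time. The fluids themselves and the sample size do not change. Masking will be imperfect, since the volumes differ and may be noticed. Even so, not telling endoscopists the arm removes the most direct route to bias at almost no cost.
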